## Abstract

**Background:**

Although the wound-healing period for purse-string closure (PSC) after stoma reversal is longer than that required for the primary closure method, the rate of wound infection is reduced. The application of negative-pressure wound therapy (NPWT) can reduce the healing period for many types of wounds. Herein, we describe a planned trial to test the hypothesis that NPWT can reduce the healing period for PSC after stoma reversal.

**Methods/design:**

Patients undergoing stoma reversal will be recruited and allocated into intervention and control groups, with 1:1 randomisation. Patients in the control group will receive standard postsurgical wound care; patients in the intervention group will receive NPWT using the PICO™ system. The target sample size will be 38 patients, as this will provide 80% power at the 5% level of significance to detect a 7-day reduction in the wound-healing period in the intervention group compared to that in the control group. The primary endpoint will be the duration to wound healing, defined as the time to nearly complete epithelisation of the wound, without any discharge or surgical site infection (SSI). Secondary endpoints will be the SSI rate, length of postoperative hospital stay, number of wound dressings and visits to the hospital for wound dressing after discharge, total cost of wound dressings, and patient and observer scar assessment scale scores.

**Discussion:**

The results of this planned randomised controlled study will clarify the role of NPWT in patients undergoing stoma reversal and strengthen the rationale for choosing a dressing technique.

**Trial registration:**

Clinical Research Information Service (CRIS), KCT0004063. Registered on 6 June 2019.

## Background

Surgeons form temporary stomas to prevent disastrous complications due to anastomotic leakage after colorectal resection, or to maintain bowel continuity in challenging cases of emergency bowel surgery. Patients with a temporary stoma generally undergo reversal surgery a few weeks to several months later. However, stoma reversal surgery has various complications, with the most common being surgical site infection (SSI) [1]. Stoma site closure is generally classified as a class 3, clean-contaminated wound, which has a high risk of SSI [2, 3]. Indeed, the incidence of SSI in cases of primary closure of the skin after stoma reversal is as high as 40% [4, 5].

The purse-string closure (PSC) method was developed in an effort to reduce the rate of SSI at the stoma reversal site, and is now widely used for skin closure after stoma reversal surgery (Fig. 1). In two previous randomised control trials (RCTs), the SSI rate was lower in patients who underwent PSC after stoma reversal than in those who underwent conventional linear closure after stoma reversal (0% vs 36.1% and 2% vs 15%, respectively) [6, 7]. Furthermore, a meta-analysis of four RCTs reported significantly fewer instances of SSI with PSC than with conventional primary closure (risk difference, − 0.25; 95% confidence interval, − 0.36 to − 0.15; *p* < 0.00001) [8]. Thus, the SSI rate decreases dramatically when PSC is used for skin closure after stoma reversal.

**Fig. 1 Fig1:**
[figure not shown]
Purse-string suture after stoma reversal

However, a hole 0.5–1 cm in diameter is formed during the PSC method for discharge drainage, and secondary healing of this skin hole is induced. Thus, a disadvantage of PSC is that the wound-healing period is prolonged compared to that for primary closure. Specifically, the mean wound-healing time is 2 weeks in patients who undergo primary closure of the skin and do not develop an SSI, but is 3.8 weeks in patients who undergo PSC after stoma reversal [6].

Negative-pressure wound therapy (NPWT) was first introduced in 1997 [9]. Since then, NPWT has been applied to various types of wounds worldwide, and numerous studies have shown its effectiveness in reducing the SSI rate and promoting wound healing [10–12]. A Cochrane Review published in 2018 specifically noted that the application of an NPWT device reduces the wound-healing period in the treatment of diabetic feet [13]. We hypothesised that the application of NPWT would similarly reduce the wound-healing period, as well as the SSI rate, in patients undergoing PSC after stoma reversal. Therefore, we designed a study, described herein, to evaluate the efficacy of NPWT in reducing the wound-healing period for PSC after stoma reversal.

## Method

### Study design

A single-centre RCT will be conducted. The wound-healing period with the application of a NPWT device after stoma reversal using the PSC method will compared to that with a conventional dressing. The study design follows the recommendations of the Standard Protocol Items: Recommendations for Interventional Trials (SPIRIT) guidelines. The study flowchart is shown in Fig. 2 Fig. 4 Additional file 1.

**Fig. 2 Fig2:**
[figure not shown]
SR-PICO study flowchart. The anticipated number of patients assessed for eligibility is based on the mean number of stoma reversal cases per year (*n* = 22) at our institution. ITT intention to treat, PICO PICO™ system, PP per protocol

### Study population

Patients aged > 20 years who will receive a temporary stoma in a stoma-reversal surgery will be recruited at Yeungnam University Medical Center in South Korea. Patients with a skin disease, including allergies that would interfere with the application or evaluation of the NPWT device, an inability to express himself/herself due to conditions such as dementia and intellectual disabilities, and an inability or unwillingness to provide informed consent will be excluded.

### Endpoints

The primary endpoint will be the duration of wound healing, defined as the time to nearly complete epithelisation of the wound, without any discharge or SSI, which is similar to the definition used in the study by Uchino et al. [3]. The determination of the degree of wound healing will be made by the researcher and a single wound/ostomy-specialised nurse. Another colorectal surgeon (who will be blinded to the patient’s identity and treatment assignment) will also judge the extent of wound healing via photographs of the wound. Wound healing will be considered complete by the consensus of all three reviewers.

Secondary endpoints comprise the SSI rate, length of postoperative hospital stay, number of wound dressings and visits to the hospital for wound dressing after discharge, total cost of wound dressings, and patient and observer scar assessment scale (POSAS) scores [14]. The presence of an SSI will be decided by the researcher and wound/ostomy-specialised nurse, using the Center for Disease Control definition of SSI [15]. The evaluation of SSI will be performed using the same process as that for the assessment of wound healing. The POSAS will be completed at the outpatient clinic approximately 1 month after surgery.

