### Data collection and management

All data for this trial will be collected after obtaining informed consent from the participants 1 day before surgery. Paper case report forms will be used to record all baseline demographics and other data for each participant. Serial wound photographs will be taken by the investigators during dressing changes, from the immediate postoperative day to the discharge day during hospital stays, and at every visit to the outpatient clinic. The photographic data will be used to determine the degree of SSI and wound healing. All photographic data will be kept on file in an anonymised fashion, in the same manner as for the patient’s other data. All information acquired in this study will be anonymised through the assignment of a trial identification number, which will be used only for this trial and its research purposes, and will only be accessible to authorised persons. All data will be stored for 3 years from study completion.

All collected data and the participant’s safety will be monitored by a data and safety monitoring committee. The committee will meet once a year to monitor the study. Because of the proven safety of NPWT, the study is expected to be safe for the participants. Nevertheless, the investigators will monitor the participants for any severe adverse events related to the study treatment (e.g. a severe skin allergy due to the dressing materials) and will immediately report these to the data and safety monitoring committee. The investigators will change the study protocol according to the recommendations of the committee.

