Although we designed this trial as a prospective RCT, several limitations exist. First, this will be a single-centre study, with a small sample size. However, we believe that the study will be adequately powered to evaluate the primary endpoint. Additionally, single-centre studies have advantages with respect to data collection consistency. Second, the assessment of the wound-healing period as a primary endpoint is subjective in nature. We plan to overcome this issue by utilising three experts to evaluate the wound directly or via photographs of the wound. However, two of the wound reviewers cannot be blinded, as one is the operator and the other is the nurse who will dress the wounds. Only one surgeon, who will evaluate the wound based on photographs, can be blinded. Third, we will enrol all types of stoma reversal surgeries, regardless of the patient’s stoma type (e.g. loop ileostomy, loop colostomy, end colostomy, etc.). This may lead to a large bias in the study; however, we believe that the inclusion of all stoma types will benefit the generalisability of the results. The stoma reversal technique will be performed in the same manner regardless of the stoma type, and the endpoints of the SR-PICO study will be limited to the evaluation of the wound at the stoma reversal site.

In conclusion, the SR-PICO trial is a planned RCT to evaluate the efficacy of NPWT in reducing the wound-healing period in patients who undergo stoma closure using the PSC method. We believe that the results of the SR-PICO trial will clarify the role of NPWT in patients undergoing stoma reversal and strengthen the rationale for choosing a dressing technique.

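### The observer scar score is left out of the blinded photograph reading used for healing and infection, so it is probably unblinded; the existing reader could score its visible items

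*Protocol article*

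**What the plan says.** All places are in the protocol article.

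- **Endpoints, status of the scale.** The last items in the list of secondary endpoints are "total cost of wound dressings, and patient and observer scar assessment scale (POSAS) scores". The scale has a patient part and an observer part.
- **Endpoints, setting.** "The POSAS will be completed at the outpatient clinic approximately 1 month after surgery". The observer is not named and masking is not mentioned.
- **Endpoints, blinded reading.** For healing: "Another colorectal surgeon (who will be blinded to the patient’s identity and treatment assignment) will also judge the extent of wound healing via photographs of" […]. Then: "Wound healing will be considered complete by the consensus of all three reviewers". For SSI: "The evaluation of SSI will be performed using the same process as that for the assessment of wound healing". There is no matching sentence for POSAS.
- **Data collection and management.** Photographs are taken during the hospital stay and "at every visit to the outpatient clinic". The stated use of the photographs is to judge SSI and healing; scar scoring is not listed.
- **Discussion, limitations.** "two of the wound reviewers cannot be blinded, as one is the operator and the other is the nurse who will dress the wounds". And: "Only one surgeon, who will evaluate the wound based on photographs, can be blinded". Both sentences belong to the limitation on the healing endpoint; the scar score is not mentioned there.
- **Statistical analysis.** Secondary endpoints are compared between arms at p < 0.05.

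**The concern.** The trial has three wound outcomes that depend on an assessor's judgement: healing, SSI and the observer part of POSAS. The article gives the first two a blinded reader and sends the third to the clinic without one. The dressings look different and are changed on different schedules (daily in the control group, twice weekly in the intervention group), so staff who have treated the patient will know the arm.

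If the observer knows the arm, even a modest leniency towards one dressing would appear as a difference in scar quality. Nothing described in the article would separate that from a real difference. The patient part is self-rated, and no photograph reading could blind it, so the point concerns the observer part only.

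**Working it through.** **1. Where the blinded reader is used.**

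| Outcome | Blinded photograph reading described? | Photograph use listed? | Unblinded assessment acknowledged? |
|---|---|---|---|
| Wound healing | Yes, as one of three consensus reviewers | Yes | Yes |
| SSI | Yes, by extension of the same process | Yes | Not separately |
| POSAS, observer part | No | No | No |

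**2. Is the observer unblinded?** The article does not say. It identifies two wound reviewers who cannot be blinded and one who can, and that one works from photographs. POSAS is completed in clinic and no other masked person is described. Unblinded is the likely reading, but it is an inference.

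**3. Is there a photograph to read?** None is named for the 1-month point. However, photographs are taken at every outpatient visit and POSAS is completed at such a visit, so one is implied. Twice-weekly follow-up is scheduled only until healing, so for a patient who heals earlier the photograph depends on the POSAS visit itself.

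**4. Group sizes.** Inputs from the Sample size calculation section: difference 7 days, SD 7 days, two-sided 5%, power 80%, attrition 10%. The standardised difference is 7/7 = 1. A two-sample t test needs 16.7, so 17 per arm. Then 17/(1 − 0.10) = 18.9, so 19 per arm and 2 × 19 = 38 in total. The plan's figure is reproduced, and nothing in this point changes it.

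**5. What a rater shift would do (illustration only).** The documents give neither a POSAS SD nor a rater bias, so the shift *b*, in SD units, is assumed. With no true difference and *n* per arm, the t statistic has a noncentral t distribution with df = 2*n* − 2 and noncentrality δ = *b* × √(*n*/2). The false-positive rate is P(|T| > t at 0.975).

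| Assumed shift *b* | δ, n = 17 | Rate, n = 17 | δ, n = 19 | Rate, n = 19 |
|---|---|---|---|---|
| 0 | 0 | 5% | 0 | 5% |
| 0.2 SD | 0.58 | 8.7% | 0.62 | 9.2% |
| 0.3 SD | 0.87 | 13.6% | 0.92 | 14.7% |
| 0.5 SD | 1.46 | 29.3% | 1.54 | 32.3% |

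These rates would hold for any endpoint with the same assumed shift. They show sensitivity to bias; they do not show that such bias is present in this trial.

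**The case against.** The strongest reply is that the article never says the observer is unblinded. The sentence about the one surgeon who can be blinded concerns the reviewers of wound healing. A separate masked clinic observer is neither stated nor excluded, and a condensed article may leave the identity of a secondary-endpoint rater to the full protocol. This stands: a reader might infer that the scar comparison certainly rests on unblinded raters, and the text supports only that it probably does. What remains is that this article does describe assessors and masking for the other two wound outcomes and leaves the blinded reading out for this one.

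Four further points have force.

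- The process for healing and SSI is not itself blinded. It is a consensus of three, two of whom know the arm. Only one reading is blinded.
- The Discussion's expectation of positive results might be taken as evidence that scar raters would favour negative-pressure therapy. In context it concerns healing time and the smaller skin opening, so it does not support that.
- A real difference in appearance at 1 month is plausible if the trial's hypothesis holds. With the planning values (19 ± 7 and 26 ± 7 days) and an assumed normal distribution, the share unhealed at day 30 is P(Z > 11/7) = 6% and P(Z > 4/7) = 28%. The illustration assumes no true difference. A blinded reading would keep a real difference and remove only the part due to knowing the arm. It would not resolve the fact that some wounds are still open when scored.
- Replacing the in-person observer score with a photographic subset would give up a complete rating for partial masking. That is a trade-off and not a correction, and it is why the photographic score should be added to the clinic score and not substituted for it.

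**Conclusion.** The point holds as a cheap improvement to a secondary endpoint. As written, the observer part of POSAS receives no blinded rating, although a blinded reader exists and a photograph at the relevant visit is implied. The clinic observer is probably unblinded, and the limitations do not acknowledge this for the scar score.

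The conclusion rests on two inferences: that no masked clinic observer is described elsewhere, and that the photographs at every outpatient visit include the POSAS visit. The size of any bias is unknown. The rates of about 9% to 29% (17 per arm) or 9% to 32% (19 per arm) depend wholly on assumed shifts of 0.2 to 0.5 SD and should not be read as predictions. The primary endpoint, the sample size of 38 and the 5% level are untouched.

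**What to change.** 1. In Endpoints, state who completes the observer part of POSAS and whether that person is masked.
2. In the same section, have the existing blinded surgeon also score the visually assessable observer items from the anonymised photograph of the roughly 1-month POSAS visit. List those items in advance. Take the photograph with the dressing off, since a visible dressing would reveal the arm.
3. In Data collection and management, add scar scoring to the stated uses of the photographs.
4. Compare the blinded score between arms alongside the full clinic observer score. Report the clinic score (unless that rater is masked) and the patient score as unblinded, and say so in the limitations.

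The cost is a few minutes per patient of a reader already in the trial, using photographs already planned. The remaining gap is that items needing touch have no blinded cover.

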### Interventions

All participants will be randomised to either the intervention group or the control group, using a 1:1 ratio. The randomisation allocation will be generated using a computerised randomisation system and applied immediately after fascia occlusion to avoid a performance bias.

Stoma reversal will be performed using standard techniques, with the patient under either spinal or general endotracheal anaesthesia, and the bowel anastomosis will be either stapled or hand sewn at the discretion of the surgeon. After fascia closure, skin closure will be performed with the PSC method using absorbable monofilament suture material (2–0 Monocryl; Ethicon, Cincinnati, OH, USA), leaving an opening ≤ 0.5 cm (approximately). Subsequently, a simple, transparent, waterproof dressing will be applied to patients in the control group, and a PICO™ portable NPWT device (Smith & Nephew Healthcare, Hull, UK) dressing will be applied to patients in the intervention group (Fig. 3).

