## Discussion

The primary objective of this RCT will be to evaluate the application of NPWT to PSC after stoma reversal regarding its effectiveness in reducing the wound-healing period.

Several mechanisms contribute to the efficacy of NPWT. NPWT reduces seroma formation in a wound and stimulates angiogenesis and granulation. Negative pressure also creates a hypoxic environment in a wound, resulting in the upregulation of inflammatory cytokines, which stimulates wound healing [10, 16].

One previous RCT evaluated the application of NPWT to laparotomy wounds following abdominal surgery [10]. In this previous study, the prophylactic use of NPWT reduced the SSI rate compared to that in the control group. However, the study did not compare the wound-healing period between the two groups. Two additional studies evaluated the application of NPWT to ileostomy closure sites and demonstrated the efficacy of NPWT in reducing the SSI rate [17, 18]. However, these previous studies focused on patients with primary linear closure of stoma wounds and did not evaluate the wound-healing period.

Uchino et al. [3] conducted an RCT with a similar primary endpoint to that in the present planned trial. The authors failed to demonstrate the efficacy of NPWT in significantly reducing the wound-healing period. However, the participants of this previous RCT comprised patients with ulcerative colitis, and the opening of the PSC was wider (8 mm) than that in the present planned trial (< 5 mm). As the opening of the PSC in the present planned trial will be ≤ 0.5 cm, we believe that our trial will more likely demonstrate positive results, which may be generalised to clinical practice. Another strength of our planned trial is that we will evaluate the cost of the wound dressings, number of wound dressings, and number of hospital visits for wound dressings after discharge, as direct and indirect assessments of the convenience level and medical cost.

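### The allocation is applied after fascia closure but before the purse-string skin closure, so the guard against performance bias stops one shared operative step too early

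*Protocol article*

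**What the plan says.** The Interventions section of the Protocol article says that a computerised system generates the allocation and that it is "applied immediately after fascia occlusion to avoid a performance bias". The next paragraph gives the order of the remaining steps. "After fascia closure, skin closure will be performed with the PSC method", with the same suture material for everyone, "leaving an opening ≤ 0.5 cm (approximately"). Then: "Subsequently, a simple, transparent, waterproof dressing will be applied to patients in the control group", while the intervention group receives the portable negative-pressure device.

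Under Endpoints, the primary endpoint is the time until the wound has almost fully epithelised, with no discharge and no surgical site infection. The Discussion compares the trial with an earlier randomised trial that had a similar endpoint and found no significant shortening of healing. It names two differences: the earlier patients had ulcerative colitis, and "the opening of the PSC was wider" (8 mm, against under 5 mm here). It then gives the smaller opening as the reason to expect a positive result this time.

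**The concern.** The stated purpose of the timing rule is to stop knowledge of the arm from influencing how the operation is done. The arms differ only in the dressing, so nobody needs the allocation until the skin is closed. As written, it is applied while one operative step, common to both arms, is still to come. That step determines the size of the hole that must heal by secondary intention, and the Background attributes the longer healing of purse-string wounds to this hole.

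If knowledge of the arm led, even unconsciously, to a slightly tighter or looser purse-string in one group, the difference would enter the primary endpoint and could not be separated from the effect of the dressing. Later safeguards would not remove it. The blinded photograph reader would correctly record a real difference in healing, and the intention-to-treat analysis would carry that difference through. The article describes no measurement of the opening, so an imbalance could not be seen afterwards.

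**Working it through.** **Order of steps (Interventions)**

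| Step | Same in both arms? | Position relative to the allocation |
|---|---|---|
| Stoma take-down, anastomosis, fascia closure | Yes | Before: protected |
| Allocation applied | – | – |
| Purse-string skin closure, residual opening set | Yes | After: not protected |
| Dressing | No, first step that differs | After: has to be |

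Only the third row is exposed without need.

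**Room for discretion at that step.** The opening has an approximate upper limit of 0.5 cm and no lower limit. The limit narrows the operator's choice but does not remove it.

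**Relevance to the endpoint.** The Background links the prolonged healing to the opening. The Discussion uses opening size to explain why this trial may succeed where another did not. A factor thought relevant between trials should be kept independent of the arm within this one.

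**Plan's own figure.** The Sample size section assumes 19 ± 7 against 26 ± 7 days, two-sided 5%, 80% power and 10% attrition.

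- Standardised difference: 7/7 = 1.0.
- Two-sample t test: 16.71, rounded up to 17 per arm.
- Attrition: 17/(1 − 0.10) = 18.9, rounded up to 19 per arm, or 38 in total.

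The stated 38 is reproduced. Changing when the allocation is revealed alters none of these inputs.

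**Illustration with assumed shifts.** The document gives no relation between opening size and healing time, so the shifts below are assumptions that only show how sensitive a trial of this size is. Suppose the dressing has no effect and a difference in skin closure moves mean healing in one arm by b days. With SD 7 and 17 evaluable per arm, the t test has 32 degrees of freedom and noncentrality (b/7) × √(17/2) = (b/7) × 2.915.

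| b (days) | b/7 | Noncentrality | Chance of two-sided p < 0.05 |
|---|---|---|---|
| 0 | 0 | 0 | 5% |
| 1 | 0.143 | 0.42 | 7% |
| 2 | 0.286 | 0.83 | 13% |
| 3 | 0.429 | 1.25 | 23% |

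Nothing in the document says which row, if any, applies.

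**The case against.** The rule does real work. It keeps the arm unknown through most of the operation, including the anastomosis, whose technique is expressly left to the surgeon. A reader might infer that the safeguard fails altogether. The text does not support that: the safeguard is incomplete, not ineffective.

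The article also does not say who learns the allocation, or at what moment. That the operator knows it while tying the suture is the natural reading of the word applied, but it is an inference. The Discussion's remark that "two of the wound reviewers cannot be blinded, as one is the operator and the other is the nurse who will dress the wounds" concerns outcome assessment and does not settle what is known at skin closure. This objection stands as a limit on certainty. It does not remove the need for a change, because if the operator is in fact kept unaware until the skin is closed, the sentence should say so.

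The closure is largely standardised: same method, same suture, same upper limit. A bias needs a systematic difference within that limit, and nothing in the article suggests one or gives it a direction. The Discussion's comparison of 8 mm with under 5 mm is between trials, is one of two differences offered, and says nothing about variation of a millimetre or less.

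A reader might go further and scale healing time by diameter: 4 mm instead of 5 mm is 20% less, and 20% of 26 days is 5.2 days, most of the 7-day target effect. The document does not support this. It would need a mean difference of 1 mm across a whole arm, healing time strictly proportional to diameter, and a 5 mm opening behind the 26 days. That control time comes from a previous trial whose opening size is not given, and the Background describes purse-string openings in general as 0.5–1 cm. The endpoint also requires absence of discharge and infection, so it is not edge advance alone.

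Finally, the operator's later role as a healing assessor is a separate matter of detection bias. The Discussion already acknowledges it, and the required agreement of a blinded surgeon partly mitigates it. It adds no weight here.

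**Conclusion.** The point holds as a gap in the timing rule. The allocation is applied one shared step earlier than the design requires, and that step bears on the primary endpoint. The conclusion rests on reading the two Interventions paragraphs in sequence and on the natural, though unstated, assumption that the operator learns the arm when the allocation is applied. The size and direction of any bias cannot be derived from the document, and the 1- to 3-day shifts above are illustrations only. The change should be made because the exposure is avoidable at little cost. It is not a defect that the trial cannot proceed without correcting.

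**What to change.** Replace the timing statement in Interventions with: *The allocation is revealed only after the purse-string suture has been tied and the residual opening has been measured and recorded, immediately before the dressing is applied.* Apply it from the next patient. Seven patients had been enrolled by 22 October 2019, so if the target of 38 is met, up to 31 could be covered from that date. Those already enrolled remain in the trial and in the analysis.

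Report the recorded opening by arm as a balance check. Keep the planned primary test (Student's t or Mann–Whitney). Adjustment for the opening is at most an optional sensitivity analysis in patients who have a measurement. As the primary analysis it would replace the planned test, and no measurement is described for the patients already enrolled.

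Cost: the allocation is opened a few minutes later, and the case report form gains one measurement. The sample size does not change.
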